### **3.2 RANDOMIZATION METHOD**

Randomization will be in a 2:1 ratio in favour of the mrTRG directed management arm. Randomization will be stratified to avoid differences between arms in important prognostic variables. Stratification variables include:

- recruiting site
- extramural venous invasion on MRI (mrEMVI grades  $\leq 2$  versus  $>2$ )
- tumour height (on MRI, height of tumour from anal verge  $\leq 6$  cm versus  $> 6$  cm)
- the planned choice of systemic chemotherapy (CAPOX/FOLFOX, versus single agent 5-FU/capecitabine)

### **3.3 RESTAGING MRI REPORTING AND INTERVENTION ARM SUB-GROUPS**

Patients should undergo the restaging MRI 4-6 weeks (maximum of 10 weeks) following completion of their initial pre-operative CRT therapy with planned surgery in the control arm at 6-12 weeks and commencement of further consolidation therapy in the interventional arm within 12 weeks.

The radiologist will be trained to report the MRIs according to synoptic proforma reporting with specified templates:

**CONTROL ARM POST-TREATMENT MRI CRF** - there is currently a lack of surgical equipoise to change operative approach based on post treatment MRI assessment. Therefore the operative decision in the control arm will be determined by the baseline MRI. Post-operative adjuvant therapy will be offered to patients based on baseline MRI features of high risk.

**INTERVENTION ARM POST-TREATMENT MRI CRF** – synoptic reporting will be performed according to the MRI form. The MRI form for the intervention arm has an additional datafield for mrTRG reporting. The mrTRG result should be discussed at the MDT:

**For mrTRG 1&2 (good response)** - deferral of surgery should be offered to the patient, with chemotherapy offered if high risk features were present on the baseline scans.

**For mrTRG 3-5 (poor response)** – 12 weeks of consolidation therapy will be offered, followed by a restaging MRI prior to a decision regarding surgery.

## **4. FEASIBILITY TRIAL OBJECTIVES AND END POINTS**

The feasibility trial is intended to inform design of a phase III trial. We need to determine the feasibility and safety of deferring surgery, and for poor responders, the acceptability of offering additional pre-operative chemotherapy.

### **4.1 PRIMARY OBJECTIVE OF THE FEASIBILITY TRIAL**

**Assess the feasibility of a phase III trial by assessing the patient recruitment rate.**

#### **Patient Recruitment**

We anticipate that the majority of patients eligible for TRIGGER will be identified at the multidisciplinary cancer meeting - where rectal cancer is initially identified and the decision to offer chemoradiotherapy is made. The trial design is complex and it may be difficult for patients to understand the concept of deferral of surgery. The prospect of further systemic chemotherapy after CRT may be daunting. Finally, being in the control arm and missing out on additional treatment options may cause anxiety for patients. These concerns may limit the number of patients willing to recruit to study and so objective figures are needed to determine if a larger phase III trial is plausible.

#### **Centre Recruitment**

This will assess the acceptability of the trial concept and the protocol. Many surgeons have expressed an interest in the trial because they are keen to be able to offer deferral of surgery in a standardised and controlled way. For the oncologists, offering additional preoperative treatment is also of interest. However, patients treated with deferral of surgery undergo more intensive follow-up than the current standard of

care, particularly in the first two years (Section 11.2.1). This may slightly increase the demands on surgical clinics, endoscopy and radiology services. We will record the number of units that open to recruitment.

## **4.2 SECONDARY OBJECTIVES OF THE FEASIBILITY TRIAL**

### **1. Assess response rate by comparing the reported mrTRG in the control and intervention arm**

Trial participants are randomised with stratification for the key factors that effect response (tumour height, mrEMVI and chemotherapy). Therefore the mrTRG should be similar in the control and intervention arm. In order to avoid the MDT being informed of the mrTRG in the control arm we will report the mrTRG grade in the control arm by centralised assessment. Comparison between the mrTRG in the control versus intervention arm will allow us to evaluate the amount of additional response achieved by using 'upfront' systemic chemotherapy.

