### 8.3 EXPERIMENTAL ARM – A ‘POOR RESPONSE’ TO CHEMORADIOOTHERAPY

1. **Post-CRT restaging** – The post-CRT MRI must be performed within 4-6 (no later than 10) weeks of completing CRT.
2. Radiologist completes the **INTERVENTION ARM POST-TREATMENT MRI Form – mrTRG 3 –5 reported.**
3. **mrTRG directed management results in the patient being offered additional chemotherapy before a decision is made regarding surgery.**
4. The option of **additional pre-operative chemotherapy** is discussed with the patient. **Chemotherapy** (Appendix 2) – The patient will receive 12 weeks (4 cycles of CAPOX or 6 cycles of FOLFOX); this should start within 12 weeks of CRT completion. Please complete the **CHEMOTHERAPY** and **TOXICITY Forms** at the end of each cycle i.e. at the end of each 3-weekly cycle of CAPOX (or single agent capecitabine) or at the end of each 2-weekly cycle of FOLFOX (or single agent 5-FU).
5. Following the completion of 12 weeks of chemotherapy a repeat MRI should be performed 4-6 weeks later and mrTRG reported. Ensure the Radiologist receives the appropriate reporting form – **INTERVENTION ARM POST-TREATMENT MRI Form** which includes the mrTRG data fields. The Radiologist completes the **INTERVENTION ARM POST-TREATMENT MRI Form**.

**mrTRG directed management results in the patient being offered deferral of surgery (if mrTRG improved to I or II) or proceeding to surgery (mrTRG remains III-V). The options of surgery or deferral of surgery as appropriate should be discussed with the patient.**

- If mrTRG now I or II and it is agreed that patient should defer surgery then patients should receive the remaining 12 weeks of chemotherapy as soon as possible following the repeat MRI and MDT meeting and be followed up in the same way as those in the ‘good-response’ sub-group described above and undergo the 5 year surveillance schedule detailed in Section 11.2.1.

- If mrTRG remains III-V then patient proceeds to surgery and undergoes the following:

6. **Surgery** is planned according to the baseline and post-treatment MRI and should be performed **6-12 weeks after pre-operative chemotherapy** is completed. A prepared **SURGERY Form** should be enclosed in the patient notes so that the surgeon can complete the form immediately after surgery.

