#### **Control arm versus Intervention arm: all patients**

- The pCRM rate will be compared between the control and investigation arms.
- The strength of agreement of the reported mrTRG will be tested for the site radiologist versus the central radiologist. An MRI training dataset will be used prior to site initiation and a kappa agreement of 0.7 or greater will be required for the site radiologist to be eligible to recruit to the study. The agreement between the recruiting radiologists and central radiologist scored mrTRG grades for scans acquired during the study for patients randomised to the intervention arm will also be assessed retrospectively at the end of the feasibility trial. The agreement between the recruiting radiologists and central radiologist scored mrTRG grades for scans acquired during the study for patients randomised to the intervention arm will also be assessed retrospectively at the end of the feasibility trial.
- Early (30 day) and late (up to 12 months) surgical morbidity will be reported according to the Clavien-Dindo classification
- Quality of surgery will be determined by using the mesorectal grading system and a similar system will be used for grading the quality of APE specimens (Pathology appendix). Outcomes will be compared between the control and intervention arms on an intention to treat basis.

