## **2 REPORTING PROCEDURES FOR ALL ADVERSE EVENTS**

The investigator is responsible for ensuring that all adverse events (including SAEs) observed by the investigator or reported by patients from the date of the post-CRT MRI scan is performed until 30 days after the last dose of chemotherapy is administered are properly captured in the patients' medical records (source documents). Adverse events occurring in all arms of the trial should be reported with the same diligence so that bias is not introduced to the apparent incidence of adverse events observed in the intervention arm. In addition, the investigator is responsible for ensuring that, for those patients randomised, all adverse events captured on the patients' medical records (as specified above) are reported on the CRF.

**NOTE: The rationale for commencing AE recording from the date of the post-CRT MRI rather than the date of randomization is to avoid capturing AEs during and shortly after the last two weeks of CRT i.e. those that could be possibly related to CRT rather than the IMP(s) (systemic chemotherapy) received as part of the trial, which patients do not receive until after the post-CRT MRI scan is performed 4-6 weeks after the completion of CRT.**

As per assessment schedules residual toxicity will be assessed at the 12 month clinic visit.

In the TRIGGER trial, the seriousness, causality and expectedness of all adverse events will be assessed by the principal investigator (or delegate) at the participating site. Upon receipt at the trial management centre, all SAEs will be also reviewed by the Chief Investigator and CTIMP Lead at the Royal Marsden (or delegate).

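### The between-arm mrTRG comparison in secondary objective 1 cannot show the effect of upfront systemic chemotherapy, because the only post-treatment MRI common to both arms precedes it

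*Protocol*

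**What the plan says.** Section 4.2, objective 1, first argues that stratified randomisation should balance response: "Therefore the mrTRG should be similar in the control and intervention arm". It then gives the comparison a causal purpose: "Comparison between the mrTRG in the control versus intervention arm will allow us to evaluate the amount of additional response achieved", with upfront systemic chemotherapy named as the source of that extra response. On the reader, it says that "we will report the mrTRG grade in the control arm by centralised assessment", so that the multidisciplinary team does not learn the control grade.

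On timing, section 3.3 applies to both arms: "Patients should undergo the restaging MRI 4-6 weeks (maximum of 10 weeks) following completion of their initial pre-operative CRT therapy". Appendix 1, section 2, explains why adverse events are recorded only from that scan onwards. It refers to the trial's systemic chemotherapy, "which patients do not receive until after the post-CRT MRI scan is performed 4-6 weeks after the completion of CRT". For intervention poor responders, section 8.3 adds a second scan: "Following the completion of 12 weeks of chemotherapy a repeat MRI should be performed 4-6 weeks later and mrTRG reported".

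On agreement between readers, section 14.2.2 provides that the site and central radiologists' "scored mrTRG grades for scans acquired during the study for patients randomised to the intervention arm will also be assessed retrospectively".

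**The concern.** A between-arm difference can be credited to a treatment only if the outcome is measured after that treatment in one arm and at a comparable time in the other. Here the measurement common to both arms comes before the treatment, and the measurement after the treatment exists in one arm only. The same paragraph expects the arms to be similar and then reads any difference as added response.

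A second problem sits on top of this. If the reported grade comes from a central reader in control and from site radiologists in the intervention arm, a systematic difference between readers would look like a difference between arms.

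At stake is a feasibility result that could be presented as evidence of chemotherapy response. Section 14.2.2 says the secondary endpoints will inform the phase III design, so a wrong attribution could carry forward.

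**Working it through.** The protocol gives no figure for this comparison, so there is none to reproduce. The check has two parts.

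**1. Timing, in weeks from the end of CRT**

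| Event | Control | Intervention |
|---|---|---|
| Restaging MRI (3.3, 8.1-8.3) | 4-6, maximum 10 | 4-6, maximum 10 |
| Start of trial systemic chemotherapy (8.2, 8.3; Appendix 2) | after surgery | after that MRI, by week 12 |
| Surgery (8.1, 8.3) | 6-12 | poor responders: 6-12 weeks after the pre-operative course |
| Later MRI with mrTRG | none scheduled (10.1) | repeat MRI in poor responders (8.3); mid-chemotherapy and surveillance MRI in deferral patients (8.2, 11.2.1) |

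At the restaging MRI nobody in either arm has had trial systemic chemotherapy, so its contribution to a between-arm difference is zero by design.

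For the repeat MRI in poor responders: week = chemotherapy start + 12 + (4 to 6). This takes the course as undelayed.
- Start at week 4, directly after an early MRI: 4 + 12 + 4 = 20 to 4 + 12 + 6 = 22.
- Start at week 12, the latest allowed: 12 + 12 + 4 = 28 to 12 + 12 + 6 = 30.

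The repeat scan therefore falls at about weeks 20 to 30, after the control arm's planned surgery at weeks 6 to 12. Setting it against the control restaging scan mixes chemotherapy with months of extra time, in patients selected because their first scan showed a poor response.

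**2. Reader**

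The control MRI form has no mrTRG field (7.4.1) and the control grade is central (4.2). In the intervention arm the grade is reported on the site's form (3.3), and Appendix 6 (image transfer) calls it part of the local report that guides management.

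For an illustration, let p be the good-response (mrTRG 1-2) rate by central read and p + e the rate by site read, with all disagreement in one direction. Then observed agreement is 1 − e, and chance agreement is Pe = p(p + e) + (1 − p)(1 − p − e). Setting kappa = 1 − e/(1 − Pe) = 0.7 gives

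e = 0.6p(1 − p) / [1 − 0.3(1 − 2p)].

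- p = 0.2: 0.096/0.82 = 0.117, so 20% versus 32%
- p = 0.3: 0.126/0.88 = 0.143, so 30% versus 44%
- p = 0.4: 0.144/0.94 = 0.153, so 40% versus 55%
- p = 0.5: 0.150/1.00 = 0.150, so 50% versus 65%

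The spurious difference is about 12 to 15 percentage points with no true difference. For scale, with 90 patients at 2:1 (30 control, 60 intervention), the 95% half-width is 1.96 × √[p(1 − p)(1/30 + 1/60)], which is 20.1, 21.5 and 21.9 points at p = 0.3, 0.4 and 0.5. A worst-case reader shift would be about 0.7 of that half-width.

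**The case against.** **Objective 1 names no scan.** It could mean that the arms are alike after CRT and that the last pre-surgical mrTRG under each strategy is then compared. That would be a randomised contrast of strategies, and it is a fair reading. It still includes the extra time and cannot isolate chemotherapy, so the sentence's attribution fails on this reading too.

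**The reader is not fixed for the intervention arm.** Intervention scans are also read centrally (4.2 objective 2, 14.2.2, Appendix 6), so a central-versus-central comparison is available, and a statistical analysis plan is promised. This stands in part. A reader might infer that reader and arm are inseparable; the documents do not support that. A mismatch is the natural reading of the reported grade, but it is avoidable. Likewise, a reader might infer that the mrTRG subgroups in 14.2.2 are formed from mixed reads, but the protocol does not say which read forms them.

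**The 12-15 points are a worst case.** This stands. Kappa of 0.7 is a minimum reached on a training dataset, and applying it to the 1-2 versus 3-5 split of trial scans is an assumption. If both readers had the same overall good-response rate, disagreement would produce no net shift.

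**The shared scan does not precede all chemotherapy.** Correct: CRT itself includes chemotherapy (9.1). The point concerns trial systemic chemotherapy only.

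**The consequences are modest.** This stands. Response by mrTRG is not listed in 4.4.2 and has no named between-arm test in 14.2.2.

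**Conclusion.** The attribution to upfront systemic chemotherapy is wrong as written. This follows from the protocol's own schedule and needs no numerical assumption: the shared scan precedes the treatment, and every later mrTRG reading is in the intervention arm only.

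The reader issue is a secondary weakness. As worded, the comparison would set central reads against site reads. The possible size of about 12 to 15 points rests on four assumptions: kappa of exactly 0.7, its use on the two-category split, disagreement all in one direction, and 20-50% good responders.

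A reader might infer that one central read should replace the site read everywhere. The documents do not support that. Unsalvageable regrowth is defined in section 11.3 for patients initially managed by deferral, and management follows the site read. Classifying by central read would drop a patient who deferred on a site grade of 2 but was read centrally as 3. If 30-50% of 60 intervention patients are good responders (18 to 30, assumed), one event is 1/30 = 3.3% to 1/18 = 5.6%, so a few reclassified patients could decide which side of the 5% criterion in 14.2.2 the result falls on.

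Overall this should be corrected, but its impact is limited: the comparison is descriptive and drives no go/no-go rule.

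**What to change.** In section 4.2, objective 1:
- Delete the statement that the comparison evaluates added response from upfront systemic chemotherapy.
- Restate the objective as a descriptive between-arm comparison of response to CRT, using the central read of the first post-CRT MRI in both arms. The expected difference is then zero, and it serves as a check of balance.
- Report post-chemotherapy mrTRG as the centrally read change from the first post-CRT MRI to the repeat MRI in intervention poor responders, labelled within-arm and uncontrolled.

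In section 14.2.2:
- For the between-arm comparisons of pCRM involvement (mrTRG 1-2) and grade 3-5 toxicity (mrTRG 3-5), define the subgroups by the central read in both arms.
- Keep the site read for management, for the agreement analysis and for the unsalvageable-regrowth proportion, and state that the denominator of that proportion is the patients actually managed by deferral.

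The cost is wording. Central reads of control scans are already specified and those of intervention scans are already planned for the agreement analysis. No patient's treatment or scan schedule changes.

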### **2. Evaluate the reproducibility of mrTRG by assessing the strength of the agreement between the recruiting radiologists and central radiologist**

A prerequisite to opening a site is that the allocated radiologist is able to perform MRIs according to the published protocol and achieve a high Kappa agreement ( $k \geq 0.7$ ) with a training dataset that includes mrTRG grades and radiological evidence of regrowth. The central MRI review will also be used to identify any missed 'radiological regrowths' using the MRI training dataset. The agreement between the recruiting radiologists and central radiologist scored mrTRG grades for scans acquired during the study for patients randomised to the intervention arm will also be assessed retrospectively at the end of the feasibility trial.

### **3. To evaluate safety by assessing acute drug toxicity and 30 day surgical morbidity**

The acute drug toxicity and the surgical morbidity will be reported descriptively and the adverse events will be discussed by the DMEC.

### **4. Compare the pCRM involvement rate in the control versus intervention arm**

The overall pCRM involvement rate between the control and intervention arms will be assessed according to an intention to treat analysis. This will be important for assessing the safety of the mrTRG directed approach. We hypothesise that a greater proportion of downstaging in the intervention arm will result in relative reduction in the overall rate of pCRM involvement compared with the control arm. The rate of inoperable regrowth occurring in patients that are managed by deferral of surgery will be specifically considered.

### **5. Compare the quality of surgery in the control and intervention arms, this will include patients who deferred surgery but later develop tumour regrowth and subsequently undergo surgery.**

### **6. Treatment plan concordance and completion rates**

To inform the sample size calculation for the main study information regarding the concordance and compliance with the treatment plan discussed at the each patient's MDT meeting prior to CRT will be assessed and captured on the CRF.

### 4.3 EXPLORATORY OBJECTIVES

Exploratory objectives include assessing the correlation between mrTRG and pathological TRG and the correlation between mrTRG and proliferative, apoptotic and genomic markers. This may help to identify the biological and genetic characteristics of chemosensitivity / chemoresistance tumours and determine whether a better pathology grading system could be developed which may need to incorporate apoptosis and proliferative indices.

### 4.4 TRIAL ENDPOINTS

#### 4.4.1 PRIMARY ENDPOINT

The total number of patients randomised per month during the last 4 months of recruitment.

#### 4.4.2 SECONDARY ENDPOINTS

- The pCRM rate will be compared between the control and investigation arms.
- The strength of agreement of the reported mrTRG will be evaluated between the site radiologist versus the central radiologist at site initiation and at the end of the feasibility trial.
- Acute toxicity will be recorded to CTCAE v4.0 protocol. The grade 3- 5 adverse events will be compared between the control and intervention arms on an intention to treat basis.
- Early (30 day) and late (up to 12 months) surgical morbidity will be reported according to the Clavien-Dindo classification
- Quality of surgery will be determined by using the mesorectal grading system and a similar system will be used for grading the quality of APE specimens (Pathology appendix). Outcomes will be compared between the control and intervention arms on an intention to treat basis.

### 4.5. OBJECTIVES OF MAIN PHASE III TRIAL

Should feasibility be confirmed the **primary objective of the Phase III trial** will be to evaluate 3-year disease free survival in patients with locally advanced rectal cancer by using mrTRG directed management to selectively offer surgery and additional pre-operative chemotherapy. There will several important secondary endpoints including an evaluation of the effect that mrTRG directed management has on quality of life.

## 5. SITE REQUIREMENTS AND ELIGIBILITY

### 5.1 STUDY SETTING

This is a multicentre trial with an anticipated 10-15 sites being involved in the feasibility stage of the trial. It is also anticipated that a limited number of these sites will be based outside the UK.

### 5.2 SITE REQUIREMENTS AND ELIGIBILITY

For a site to be identified as eligible for participation the TRIGGER Trial they will be required to:

- Complete a Site Feasibility Form, Contacts Log and Delegation Log for assessment by trial staff at the TRIGGER Trial Office.
- Be able to meet the research and development requirements of their institution.
- Be able to demonstrate a potential for recruiting suitable subjects – sites will be asked to provide details about the target population at their site, including the number of potentially eligible patients the investigator treats.
- Ensure that each patient recruited is discussed at a multidisciplinary team meeting – that includes a minimum of 1 oncologist, 1 pathologist, 1 radiologist and 1 surgeon.
- Have a nominated appropriately qualified individual responsible for pharmacovigilance. In most cases this will be the local Principal Investigator, however pharmacovigilance can be delegated to a medical oncologist if the site PI is a surgeon. This should be documented on the site Delegation Log.
- Agree that the nominated GI Radiologist will complete an MRI Reporting workshop/webinar detailed in Section 5.2.1.
- Comply with the MRI and Pathology proformas.
- Accommodate and be able to deliver all aspects of the protocol, including patient follow-up, particularly the follow-up requirements for safe deferral of surgery.
- Provide contact details for all trial personnel at the participating site. Names and addresses of all participating principle investigators is a requirement of MHRA approval so it is vital this information is received by the trial staff at the Royal Marsden. The trial office must be notified of any changes to trial personnel and/or their responsibilities during the trial. An up-to-date copy of the delegation log can be faxed to the trial office for this purpose and the up-to-date log stored in the trial investigator site file.

- Once the Site Feasibility Form, Contacts Log and Delegation Log are received and assessed at the TRIGGER Trial office, the participation site must apply for their local R&D approval. At the same time the following documents will be required prior to site initiation:
  - A signed Clinical Trial Agreement between the Royal Marsden NHS Foundation Trust and the site.
  - CV of Principle Investigator and co-investigators and evidence of GCP training (or confirmation these are held on site).

